## Abstract

**Background:**

When a Zuni elder sustains a fall-related injury, the closest tribal skilled nursing facility is 100 miles from the Pueblo and no physical therapy services are available. Thus, fall prevention strategies as a primary intervention to avert injurious falls and preserve aging in place are needed. The objective of the study is to compare the effectiveness of a community health representative (CHR)-delivered, culturally-adapted Otago Exercise Program (OEP) fall prevention program compared to the standard of care education-based fall risk management.

**Methods:**

“Standing Strong in Tribal Communities: Assessing Elder Falls Disparity” is mixed-methods research with a randomized controlled trial. The CHRs will be trained to deliver the culturally-adapted OEP trial and offer advantages of speaking “Shiwi” (Zuni tribal language) and understanding Zuni traditions, family structures, and elders’ preferences for receiving health information. Focus groups will be conducted to assure all materials are culturally appropriate, and adapted. A physical therapist will train CHRs to screen elders for falls risk and to deliver the OEP to the intervention group and education to the control group. Up to 400 Zuni elders will be screened by the CHRs for falls risk and 200 elders will be enrolled into the study (1:1 random allocation by household). The intervention is 6 months with measurements at baseline, 3, 6 and 12 months. The primary outcome is improved strength and balance (timed up and go, sit to stand and 4 stage balance test), secondary outcomes include falls incidence, self-efficacy using Attitudes to Falls-Related Interventions Scale, Medical Outcomes Study Short Form 12 (SF-12v2) and Self-Efficacy for Managing Daily Activities.

**Discussion:**

Fall prevention for Zuni elders was identified as a tribal priority and this trial is built upon longstanding collaborations between the investigative team, Zuni tribal leaders, and multiple tribal health programs. Delivery by the CHRs make this model more acceptable, and thus, more sustainable long term. This study has the potential to change best practice for elder care in tribal and rural areas with limited access to physical therapist-delivered fall prevention interventions and aligns with tribal goals to avert fall-related injury, reduce healthcare disparity, and preserve elder’s independence.

**Trial registration:**

NCT04876729

## Background

A growing source of health disparities is the epidemic of falls and associated injuries in socio-economically disadvantaged and geographically isolated American Indian communities. Falls are particularly serious for older American Indians who experience more comorbidity and chronic illnesses than the general population [1]. The unintentional fall death rate is higher in American Indians from the Southwestern US than other regions of the US and is higher in New Mexico (NM) than other regions of the US [2]. The latest available data in 2017, reported that unintentional fall-related injury was the leading cause of unintentional injury-related death, hospitalization and emergency department visits for older New Mexicans [3]. A Tribal Behavioral Risk Factor Surveillance Survey of NM tribes conducted by the Albuquerque Area Southwest Tribal Epidemiology Center reported that 32% of American Indian adults 65 + experienced at least one fall in the past three months. Among those who reported a fall, 30% sustained an injury [4]. Compounding these statistics, the fall-related mortality rates increased dramatically from age 50 years, which is 15 years younger than the national trend [5]. Fall-related injuries place older adults at risk of losing independence, and the New Mexico Department of Health reports that only 25% of adults hospitalized for a fall-related injury are discharged directly home [5]. The Zuni Pueblo in New Mexico is geographically isolated with limited access to rehabilitative services. If a Zuni elder sustains a fall-related injury, the closest tribal assisted living or skilled nursing facility is 100 miles from the reservation. Thus, fall risk and rates reduction is essential for this vulnerable community.

Many falls prevention interventions focus on improving lower body function through strength, gait, and balance training, in addition to the reduction of certain medications, removing home hazards, and correcting vision impairments [6–11]. However, there is very little data on strength, balance, and lower body function in older American Indians. The only study that objectively measured lower body functioning using the short physical performance battery test (SPPB) in a South-eastern tribe of elders reported that 51.8% of the sample had a baseline score of 9 or less (mean 8.8 ± 3.3) indicating poor physical function. The score worsened with age and was negatively associated with physical inactivity, vision loss and medical comorbidities [12]. Therefore, research on adapting existing evidence-based programs to American Indians, and testing their effectiveness, is still lacking.

In this mixed-methods research with a randomized controlled trial, we will culturally tailor the evidence-based falls prevention program, Otago Exercise Program (OEP) [13–17], and Centre for Disease Control (CDC) STEADI patient education tools [18] to evaluate their effectiveness in reducing fall risk factors and preventing falls in Zuni elders. To address elder falls disparity, we will train Zuni Community Health Representatives (CHRs), rather than Physical Therapists to deliver the adapted OEP. The CHRs are paraprofessional, indigenous, community-based, and trained healthcare staff who make excellent health advocates. They speak the Zuni tribal language (“Shiwi”) and understand family structures, traditions of the Zuni people, and elders’ preferences for receiving health information. The research objective is to compare the effectiveness of an adapted OEP that is CHR-delivered compared to the standard of care, which is an education-based fall risk management approach.

Our study was designed to accomplish the following specific aims:

To foster a sustainable multi-directional, participatory collaboration between the Zuni’s tribal leadership, stakeholders, Zuni Indian Health Services, and University of New Mexico Health Sciences Centre to enhance fall prevention training, education, and research.To culturally adapt the evidence-based OEP for use with the Zuni elder population, by training CHRs to utilize the CDC STEADI toolkit for fall risk screening and the education control group.To compare the effectiveness of the adapted OEP to an education-based fall risk management program in improving strength and balance (decreasing falls risk) and reducing falls among Zuni elders.To compare the effectiveness of the adapted OEP to an education-based fall risk management program in improving overall health status, self-management of daily activities, and social engagement. 

Our proposed work is innovative by building on our collaboration with the CHRs and tribal leadership. In partnership, we will culturally adapt the OEP for use in an American Indian community, test a model of expanding the role of trained CHRs in preventing falls using OEP in people’s homes, and develop a model for fall risk reduction to expand the role of Medicaid-reimbursed CHRs.

## Methods

### Design and setting

Our overarching aim of this study is to reduce falls risk health disparity among Zuni elders and to develop research capacity and resources for the Zuni Pueblo and it’s residents. It is a mixed-methods approach with a randomized controlled trial set on the Zuni Pueblo in New Mexico and the study flow chart is depicted in Fig. 1.

**Fig. 1 Fig1:**
[figure not shown]
Flow diagram randomized controlled trial of fall prevention Iintervention

### Participant characteristics

#### Inclusion

Zuni elders will be eligible to participate if they are Zuni tribal members aged 65 years and older who demonstrate elevated fall risk according to 2 or more of the following outcomes: (1) Timed Up and Go ≥ 12 s; (2) 30 Second Chair Stand Test below age and sex norms; (3) Inability to complete the Four Stage Berg Balance Test; (4) Four or more positive responses on the *CDC Stay Independent: Check Your Risk for Falling*; or (5) history of 2 or more falls during past year or one injurious fall during past year.

#### Exclusion

The exclusion criteria include: (1) Self-reported diagnosis of terminal cancer in the last 6 months; (2) Currently on dialysis; (3) Mini-Cog score of 0 to 1; (4) Unwillingness to consent to participate; (5) Unable to walk with or without an assistive device; or (6) Legally blind. Potential participants will be screened and those eligible will be randomized into CHR-led OEP arm or an educational intervention control arm.

#### Specific aims

Aim 1 is to foster a sustainable multi-directional, participatory collaboration between the Zuni’s tribal leadership, stakeholders, Zuni Indian Health Services, and the University of New Mexico Health Sciences Centre to enhance community engagement in fall prevention training, education, and research. This will be achieved through a relationship with a Tribal Advisory Panel (TAP) that was convened and met twice to review the proposed study protocol and provided feedback and guidance to the investigators regarding conduct of the study. Liaisons from existing tribal health programs have been identified and have agreed to participate as TAP members. Community coordinators are part of the health programs at the Zuni Pueblo and will attend the quarterly TAP. The researchers based at the University of New Mexico will also attend quarterly meetings with the TAP, and discussions will focus on CHR activities and project goals. Individuals who participate on the TAP will work to ensure continuity and adherence to study timelines. A formal Manual of Procedures has been developed and the TAP will also reinforce existing data use and ownership agreements, and articulate processes for disseminating study findings. Importantly, if the falls prevention program proves successful, the tribe will enthusiastically attempt to sustain the program with support of the Senior Centre and the CHRs.

Aim 2 is to culturally-adapt the evidence-based OEP for use with the Zuni elder population. During the first 12 months, we will complete the program adaptation in three phases: (1) Provide education for CHRs to understand elder falls risks, the CDC STEADI toolkit, and OEP protocol training. The purpose is to provide CHRs with sufficient education to conduct focus groups and begin the adaption of OEP intervention and education (control arm) materials. The CHRs will convene 4 focus groups of 7–10 Zuni elders to provide feedback on the study protocol and materials. These resources will be culturally adapted to ensure possible phrasing and statements considered I:ba’naye (‘Taboo’ in Shiwi) are not used. Once the materials are adapted, the CHRs will conduct 1–2 focus groups to obtain feedback on the revised materials for the intervention (2) CHRs will work with project investigators to culturally adapt the STEADI participant resources (control arm) including home safety checklist and OEP participant manual (intervention arm) and; (3) once all relevant intervention content is revised, the CHRs will receive additional in depth training on the use of the measurement instruments, as well as the OEP protocol, materials and training/operations manual. Trained Zuni facilitators from our ongoing Zuni Health Initiative study will moderate the focus groups. Focus group discussions will be audio recorded and transcribed using NVivo.

The STEADI *Check Your Home for Safety* will be adapted in addition to the STEADI educational materials, the OEP participant manual will be adapted to (1) ensure that exercises are perceived as culturally appropriate; (2) instructions are at an appropriate literacy level; and (3) link exercise prescription to valued daily activities to improve perception of personal relevance to healthy aging [19].

Once all relevant intervention content is revised, the CHRs will receive additional in-depth training on the use of the measurement instruments, as well as the OEP protocol, materials and training/operations manual.

The education control group will receive education via the CDC *Stay Independent* checklist as part of the fall risk screening process. Additionally, the education control group will receive information from the CDC STEADI toolkit during the home visits. The education control group will review: *Stay Independent, What You Can Do to Prevent Falls, Check for Safety,* and *Postural Hypotension: What It Is and How to Manage It*. The CHRs will provide 10 min of falls prevention education per document and these resources will provide structure to CHR-delivered education and remain in people’s homes. The education control group will be assessed on the same schedule as the OEP intervention group.

All CHRs will be trained in the OEP intervention, the control group education protocol and the outcome measures. To ensure competency, four CHRs will be trained and supervised by a physiotherapist, who is experienced with implementing OEP in patient populations. The CHRs will receive comprehensive education on the use of the CDC STEADI toolkit for fall risk screening and the OEP adapted protocol. In addition, CHRs will review the online training developed by the University of North Carolina Geriatric Education Centre, “Preparing Community Health Workers and Promotors’ to Prevent and Reduce Falls Among Older Adults” [20]. The CHRs will achieve a score of 80% on a written and practicum exam for OEP, education control protocol, and home safety assessment protocol, and demonstrate competency during three simulated encounters, two initial participant encounters as well as quarterly observation of visits.

### Randomized controlled trial

#### Screening

Up to 400 elders will be screened for eligibility. If eligible, the CHRs will conduct the 3 gait, strength and balance tests and participants will complete a self-assessment for fall risk, Stay Independent, which the CHRs will review. Our pilot study used this self-assessment instrument and elders provided feedback that the questions were culturally appropriate and demonstrated willingness to provide responses [28].

#### Randomization

After the initial screening eligible and willing participants will be consented (n = 200). At that time, they will be randomly assigned to either OEP or the control education arm, stratifying within levels of fall risk (low, medium, or high) and employing cluster randomization by household family unit. Random assignment will be made according to a random allocation list that will be generated upon study initiation. This list will be generated such that sequentially consented participants will be assigned to study arms according to the falls risk of the first enrolled family member. Our intent is to obtain roughly equal numbers of participants within each of the strata defined by falls risk. To avoid contamination, we will apply a single intervention to the members of a particular household family unit. Therefore, it is possible that the number participants within a treatment group may not be perfectly balanced across falls risk strata. This will have minimal impact on the outcome of the trial, particularly relative to the contamination problems that it overcomes. Treatment groups will be assigned randomly to household family units grouped within blocks. Blocks will comprise 2 or 4 household family units, and the sequence of block sizes will be randomly generated. This dual random allocation will ensure that the study arms will remain relatively balanced while enhancing masking of treatment allocation to those enrolling study participants. The screenings will be conducted at the Zuni Health Initiative Site. We can also arrange for screening at the elder’s home if that is their preference.

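### Relatives who enrol after a household's first member can join, and be baseline-tested, with their arm already known, and the masking from random block sizes does not cover them

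*Protocol article*

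**What the plan says.** All of the enrolment rule is in the protocol article, Methods, Randomization.

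- The unit of allocation is the household: "employing cluster randomization by household family unit", stratified by fall risk.
- Assignment follows consent directly: "At that time, they will be randomly assigned to either OEP or the control education arm".
- The stratum comes from one person: the list is built so that "sequentially consented participants will be assigned to study arms according to the falls risk of the first enrolled family member".
- Everyone in the household gets the same arm: "we will apply a single intervention to the members of a particular household family unit". The stated reason is to avoid contamination.
- Concealment rests on block sizes: "Blocks will comprise 2 or 4 household family units, and the sequence of block sizes will be randomly generated". The section credits this with "enhancing masking of treatment allocation to those enrolling study participants".

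On staff roles, the Abstract states "Up to 400 Zuni elders will be screened by the CHRs for falls risk", and the Screening section states "the CHRs will conduct the 3 gait, strength and balance tests". Under Specific aims, all CHRs are trained in both programmes and in the outcome measures. Strengths and limitations says that assessment will not be blinded.

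**The concern.** In a cluster trial, allocation is concealed for a participant only if that person is identified, screened and consented before the cluster's arm is known. Here the first member's consent triggers the household's assignment, and the text allows others in the household to enrol afterwards. For them no allocation is left to conceal.

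Two things are at stake. The first is selection. An elder may join because the household is already receiving exercise visits, or decline because it is receiving education, so the later entrants in the two arms may differ in number, fitness or motivation. The second is measurement. The Timed Up and Go, chair stand and four-stage balance tests decide eligibility (Inclusion), provide the baseline (Table 1) and are the primary outcomes (Data analysis plans). A tester who knows the arm can affect both who enters and the starting point from which change is measured.

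**Working it through.** **Step 1. Order of events.** Set side by side, the rules of the Randomization section give this sequence: the first elder is consented; the household is assigned at that time, in that elder's stratum; any further elder in the household receives the same arm. A rule that refers to the first enrolled member matters only if a household can have others. Nothing in the article requires all elders of a household to be listed, screened or consented before the household is assigned.

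**Step 2. What the block sizes protect.** Blocks are made up of households. Varying their size makes the next household's arm harder to guess. It does nothing for a relative in a household that is already assigned.

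**Step 3. Who can know the arm.** The exercise arm starts with a home session of 60 to 75 minutes and has three home visits in the first four weeks (The modified OEP intervention; The OEP intervention first visit). A co-resident elder would notice. CHRs screen and test, are trained to deliver both arms, and are not blinded.

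**Step 4. How it reaches the primary test.** The primary test is the arm-by-time interaction in a linear mixed model (Data analysis plans). If a borderline performance is scored as failing so that a relative in an exercise household can enter, later recovery toward that person's usual level counts as improvement in that arm. A household term in the model corrects the standard error. It does not shift the estimate back.

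**Step 5. How many could be exposed.** The article gives no number of elders per household, so this is a range under assumptions. Let m be the mean number of participants per household and g the fraction of non-first members who enrol after assignment. Neither is stated.

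Exposed share = (1 − 1/m) × g. The upper bound, at g = 1, is 1 − 1/m.

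| Assumed m | 1 − 1/m | Upper bound, of 200 |
|---|---|---|
| 1.1 | 9% | 18 |
| 1.25 | 20% | 40 |
| 1.5 | 33% | 67 |
| 2.0 | 50% | 100 |

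If g is one half, each figure halves; at m = 1.5 that gives about 33 of 200. If g = 0 or m = 1, the number is zero.

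**Step 6. What it could do (illustration only).** Suppose exposed members differ between arms by d = 0.3 SD in the analysed change for reasons other than treatment (assumed). With exposed share f, the bias is b = f × d. With 100 per arm and ignoring clustering, SE = √(2/100) = 0.141 SD. The two-sided type I error is Φ(−z + b/SE) + Φ(−z − b/SE), where z is the critical value.

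| f (upper bound) | b (SD) | Type I error, nominal 0.05 | Type I error, nominal 0.05/3 |
|---|---|---|---|
| 0.09 | 0.03 | 0.054 | 0.019 |
| 0.20 | 0.06 | 0.071 | 0.027 |
| 0.33 | 0.10 | 0.109 | 0.047 |
| 0.50 | 0.15 | 0.186 | 0.092 |

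The last column is included because the power section corrects for three primary tests. The effect runs from negligible to material, depending on figures the article does not give.

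**The case against.** The best defence is that the article does not describe relatives arriving weeks apart. The first-member rule may only be a way of choosing the stratum, and it fits relatives who are screened and consented together. A manual of procedures exists and is not shown; it covers intake and screening, and could require the whole household to be consented first. Other features soften the risk. Both arms have the same visit schedule, and everyone is offered home safety modifications, so there is less reason to decline the education arm. Eligibility needs two of five criteria with stated cut-offs, two of which are not performance tests. Some screenings are observed. The primary test concerns change rather than level, and the analysis will be adjusted if major baseline differences appear.

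Part of this stands. A reader might infer that every non-first member is exposed, but relatives who consent together before assignment are not, so 1 − 1/m is only a ceiling. A reader might also infer that CHRs take consent. The article gives them screening and testing and does not say who consents. The point does not need that inference, because the elder and the testing CHR can both know the arm. Nor do the documents show that selection will occur; they show only that nothing stated prevents it.

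The rest does not close the route. The rule is stated in the article, together with a masking claim that cannot extend to late joiners, so this is more than a detail left out of a condensed text. A test of change is not immune, because an arm-aware baseline score is part of the change. Adjusting for measured baseline characteristics does not recover unmeasured motivation.

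**Conclusion.** The point holds as a weakness in the order of allocation and enrolment. Any relative who enrols after the household is assigned can be screened, tested and asked to decide with the arm known, and the stated masking does not reach that person. The conclusion rests on the text of the Randomization section and on CHRs being unblinded testers.

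Its size cannot be derived from the article. The ceiling is 9% to 50% of participants (18 to 100 of 200) for assumed m of 1.1 to 2.0, and the true share is lower to the extent that relatives consent together before assignment. If each household enrols one elder, or all its members consent first, the problem disappears. A claim that the trial will be biased, or that up to half of the sample is compromised, would go beyond the documents. The change should be made because the route is open and cheap to close.

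**What to change.** In the Randomization section, state that all willing elders in a household are identified, screened, consented and baseline-tested before that household's allocation is released. Set the stratum from those pre-allocation tests by a fixed rule, for example the highest-risk consenting member, in place of whoever enrolled first.

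Flag anyone who joins after allocation, report their number by arm, and prespecify a sensitivity analysis limited to members consented before allocation. Dropping late joiners from the primary analysis is a stronger option that should not be adopted without thought. The power section requires 84 per arm from 100 enrolled. At the ceiling for m = 1.25, excluding them would leave 100 × 1/1.25 = 80 per arm, and for m = 1.5 it would leave 100 × 1/1.5 = 67.

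If the manual of procedures already requires whole-household consent before assignment, a sentence saying so would settle the point. The household design and its protection against contamination are unchanged. The cost is a revised enrolment procedure and a short wait for the first member while relatives are screened.
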